### Allocation

Stratified block randomisation is conducted at the level of childcare centres, with nine centres randomised to our multicomponent intervention and nine centres randomised to care-as-usual (control). Intervention centres will receive all four components of the multicomponent intervention, control centres will provide care as usual. Stratification is based on size of childcare centres regarding number of children attending a childcare center. A small childcare center is defined as having fewer than 65 children attending childcare, while a large childcare center is defined as having more than 65 children attending childcare. The randomisation procedure is conducted by an independent researcher via http://www.randomization.com/. Childcare staff and parents will not be blinded after intervention allocation due to the nature of the multicomponent intervention. However, they are blinded to the primary outcome measure. Researchers will be blinded during data analysis to the allocation status of childcare centres.

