The decision regarding illness absenteeism due to fever and common infections may be driven by both parents and childcare staff. Elevated temperature or fever can create a range of concerns among those caring for the child. At the core of these concerns is the misconception that the temperature elevation represents the severity of underlying illness, rather than a relatively benign symptom resulting from an infectious disease. In addition, harmful consequences of fever are feared and body temperature is measured several times per day to monitor disease progression [13–25]. The term fever phobia has been used to describe an exaggerated, unrealistic and unfounded fear of fever expressed by parents, healthcare professionals and childcare staff [24]. An important driver of fever phobia is a lack of knowledge regarding fever pathophysiology, but also previous (negative) experiences, beliefs, sense of personal control, perceived threat of illness, inconsistencies in healthcare providers’ advices, and the concern of not recognising a serious illness on time [14–16, 25–29]. In turn, fever phobia influences general practitioner (GP) consultations for childhood fever [5, 6, 22, 30–33]. Similarly, fever phobia is present in childcare staff and causes substantial illness absenteeism in children, work absenteeism among parents and healthcare service consultations by referring parents to the GP [2, 6, 13, 16, 17, 20, 33–37]. Despite the development of several educational interventions, fever phobia, misconceptions and unrealistic concerns are still present in parents, healthcare professionals and childcare staff [36, 38–40].

Educational interventions on fever and common infections targeting childcare staff are scarce and focus merely on hygiene prevention [12, 30, 41–43]. These hygiene prevention interventions are successful in reducing illness incidences rates, children’s illness absenteeism and parents’ work absenteeism [12, 30, 41, 42]. However, educational interventions for childcare staff regarding fever pathophysiology, infectious diseases and self-management strategies could be beneficial for diminishing fever phobia, since childcare staff strongly influence childcare illness absenteeism, work absenteeism for parents, and parental healthcare seeking behaviour [34].

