### Development of multicomponent intervention

A multicomponent intervention was developed using IM with the aim to target underlying determinants of behavioural change of childcare staff in order to optimise their decision making with respect to illness absenteeism due to fever and common infections in childcare.

The first step of the development process was the assessment of extensive needs to explore difficulties towards childhood fever, causes, consequences and implications for practice by means of a systematic review, a survey study among parents of children visiting childcare, and three qualitative studies among general practitioners, well-child clinic professionals, and childcare staff [17, 25, 39]. Initial data analyses from the qualitative study among childcare staff showed that fever phobia was common and emanated from a lack of knowledge and education on fever and common childhood infections [unpublished observations]. Childcare staff expressed that their current knowledge was merely experience-based, both individually and as group sharing experiences, and guided by the operating protocol of their childcare organisation. An uncomfortable feeling was also expressed in case of an increase in the child’s body temperature, caused by the concern that an increased temperature would represent the severity of illness. This finding was similar to previous studies [15, 16, 18, 19, 24, 25]. In agreement with another study, data from the qualitative study demonstrated that body temperature is frequently measured to monitor illness progression gives a sense of control over the illness [14]. Like parents, childcare staff especially fear febrile seizures as a result of an elevating body temperature and irregular administration of paracetamol [16]. In response to their concerns, childcare staff prefer to exclude children with a fever from childcare and return the responsibility to the parents. In agreement with previous research [17, 34], parents are also actively advised by the childcare staff to consult the GP for a check-up.

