### Outcomes

The primary outcome is absenteeism due to illness, defined as the percentage of days that the child is absent from childcare due to illness from the total number of childcare days during a 12-week period. This primary outcome will be used to evaluate the potential behavioural change in decision making on illness absenteeism, resulting from the multicomponent intervention that was developed to target behavioural determinants such as knowledge, attitude, self-efficacy and risk perception.

Secondary outcome measures are: 1) knowledge, attitude, self-efficacy and risk perception towards fever and common infections are measured among childcare staff and parents; 2) incidence rate of fever and common childhood infections; 3) number and duration of illness episodes in children who are called in ill or sent home because of illness during the study period, and whose parents complete a survey on this illness episode; 4) work absenteeism among parents who complete a survey when their child is called in ill or sent home because of illness during the study period; 5) healthcare service use for fever and/or common infections in children who are called in ill or sent home because of illness during the study period and of which parents complete an additional survey on this illness episode, 6) paracetamol use for fever and/or common infections in children who are called in ill or sent home because of illness during the study period and whose parents complete an additional survey on this illness episode.

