#### Primary outcome measure

A standardised paper-based illness registration form is developed in close collaboration with the participating childcare organisation (see Additional file 3). Six booklets each comprising 2 weeks of childcare will be provided to all participating childcare groups for the study period of 12 weeks. Childcare staff will register childcare attendance, childcare absenteeism because of illness, and absenteeism due to other reasons (e.g. holiday) on a daily basis. When children are called in ill or sent home ill, childcare staff will register initials of the child, infection symptoms and how many days the child is (partially) absent due to illness. In addition, childcare staff in the intervention group will also record decision tool use. Childcare staff in both groups will receive training and feedback on registration during a 2-week run-in period before the actual start of the trial (see Table 1). This method of illness registration is comparable to other studies [63, 67, 68].

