## Discussion

This paper describes the development and study protocol for the evaluation of a multicomponent intervention in a cluster randomised trial that aims to improve decision making among childcare staff on illness absenteeism due to fever and common infections in childcare. The Intervention Mapping approach was used to systematically develop the intervention, according to the needs requirements of the end-users. A multicomponent intervention is developed to target the different behavioural determinants of decision making in several ways. This approach incorporated an extensive needs assessment based on results of own previous research and the available evidence from the scientific literature. The development included further a close collaboration with experts and end-users, and was pilot tested in a childcare organisation that will not take part in the main trial.

The content of the intervention is consistent with current guidelines of the Dutch College of General Practitioners, Dutch Public Health Services, and the operating protocol on illness from the participating childcare organisation. The multicomponent intervention will be evaluated in a cluster randomised controlled trial with nine childcare centres receiving the intervention and nine provide care-as-usual. There is a risk of contamination since childcare replacement staff may work in both intervention and control centres. Yet, we think this risk is minimal as the vast majority of staff works in one center only. Furthermore, to minimise this risk only permanent staff and fixed replacements will be allowed to attend the educational session. We chose to plan daily registration of absenteeism by childcare staff to minimise recall bias. Recall bias for secondary outcomes reported by parents will be minimised by sending out the survey within 2 weeks of illness of their child, followed by reminders every 3 days. Childcare staff will be blinded to the primary outcome measure to avoid bias.

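### Staff who know their arm classify every absence as illness or other, so calling them blinded to the primary outcome does not show protection against biased classification

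*Protocol article*

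**What the plan says.** All references are to the protocol article.

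- **Knowledge of arm** (Allocation): "Childcare staff and parents will not be blinded after intervention allocation due to the nature of the multicomponent intervention".
- **Claimed protection** (Allocation, next sentence): "However, they are blinded to the primary outcome measure". The Discussion repeats it for staff and gives a purpose: "Childcare staff will be blinded to the primary outcome measure to avoid bias".
- **Primary outcome** (Outcomes): "the percentage of days that the child is absent from childcare due to illness from the total number of childcare days", over 12 weeks.
- **Who records it** (Primary outcome measure, under Data collection): "Childcare staff will register childcare attendance, childcare absenteeism because of illness, and absenteeism due to other reasons (e.g. holiday) on a daily basis". For each child who is reported sick or sent home, staff also enter symptoms and the number of days missed. Both arms are trained on the form and given feedback in a two-week run-in.
- **Difference in recording between arms** (same section): "childcare staff in the intervention group will also record decision tool use".
- **Other blinding** (Allocation): researchers do not know the centres' allocation while they analyse the data.

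**The concern.** The primary outcome depends on a label, illness or other reason, which staff attach to each absence knowing their own arm. If that label, or the care with which it is applied, differs between arms, the illness percentage can differ although no child attended more. The article answers this threat with a statement about blinding, made twice and once with the avoidance of bias as its stated purpose. A reader would take from it that outcome assessment is protected, but the recording procedure gives no ground for that. If the trial reports a reduction, the reported illness figure alone could not separate more attendance from different labelling.

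**Working it through.** **1. The statements set side by side.** Staff know their arm. Staff are trained to register illness absence, and do so daily. The primary outcome is the percentage of childcare days lost to illness. It follows that staff know illness absence is being measured and produce the measurement themselves, unblinded to arm. The only thing that can still be hidden from them is its rank among the outcomes. Hiding the rank does not hide the arm or the variable, and those two are enough for differential labelling. The blinding of researchers acts on data in which the label is already fixed.

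**2. The plan's own figures (Sample size).** Inputs: control rate 9.9%, target reduction 4.5 points, SD 18.035, two-sided α 0.05 (Analysis), power 80%, 55 children per cluster, intra-cluster coefficient 0.01, and two corrections of 10%.
- Per group: 2 × (1.96 + 0.8416)² × 18.035² / 4.5² = 252.1, rounded up to 253.
- Design effect: 1 + (55 − 1) × 0.01 = 1.54, and 253 × 1.54 = 389.6, so 390.
- Corrections: 390 / 0.9 / 0.9 = 481.5, so 482.

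All three stated figures reproduce, and this point changes none of them. Planned intervention-arm rate: 9.9 − 4.5 = 5.4%.

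**3. Size of a labelling bias (illustration).** Let *m* be the share of intervention-arm illness days recorded as other absence, *p* the true illness rate in that arm, and let relabelled days stay in the denominator. The spurious reduction is *p* × *m*. The documents give no value for *m*, so the values below are assumptions.

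| *m* (assumed) | *p* = 9.9% (no true effect) | share of 4.5 | *p* = 5.4% (planned effect) | share of 4.5 |
|---|---|---|---|---|
| 10% | 9.9 × 0.10 = 0.99 points | 22% | 5.4 × 0.10 = 0.54 points | 12% |
| 20% | 9.9 × 0.20 = 1.98 points | 44% | 5.4 × 0.20 = 1.08 points | 24% |

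**4. Effect on the test when there is no true effect.** With 253 effective children per group, SE = 18.035 × √(2/253) = 1.60. The chance of p ≤ 0.05 is Φ(b/SE − 1.96) + Φ(−b/SE − 1.96), where b is the bias.
- b = 0.99: 9.5%.
- b = 1.98: 23.5%.

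The nominal level is 5%.

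**5. What all-cause absence would show.** Pure relabelling lowers illness absence by *pm* and raises other-reason absence by *pm*, so the sum does not move. A true reduction *d*, with other-reason absence unchanged, lowers the sum by *d*. The two cases can therefore be told apart, within sampling error, from fields already on the form.

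**The case against.** The strongest reply is that the sentence means something narrower: staff and parents are not told which measure is primary. Staff also record attendance and symptoms and complete a survey on knowledge and attitudes, so knowing that illness absence is registered is not the same as knowing that it is the endpoint. This reading is possible, and it is why a reader should not conclude that the statement is simply false or that no protection of any kind exists. The article does not say this, however, and the narrower reading still does not support the purpose given in the Discussion.

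Three further inferences are tempting and are not supported:
- *That staff decisions to exclude a child are part of the bias.* The Background says: "The decision regarding illness absenteeism due to fever and common infections may be driven by both parents and childcare staff". The needs assessment found that "childcare staff prefer to exclude children with a fever from childcare and return the responsibility to the parents". Those decisions are what the intervention sets out to change, and Outcomes says the primary outcome is there to capture that change. A shift in them is effect.
- *That intervention staff are taught that absence is too high.* The listed session topics are how fever arises, how it is treated, and febrile seizures, with practice of the decision tool. No section says more than that.
- *That relabelling is large or must favour the intervention.* Many illness absences start with a parent's report or a visible event, the form is standardised, and both arms are trained. Staff who also log decision tool use might record illness more fully. Neither direction nor size is established.

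It can also be said that sensitivity analyses are often left to a statistical analysis plan, which is not shown here. That is fair, and the absence of one is not the defect. The defect is a protection that the article asserts and its own procedures do not support.

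**Conclusion.** The point stands and should be corrected. The article claims, as a guard against bias, a blinding that its data collection section does not bear out: the primary outcome is recorded by people who know their arm. The bias in question is confined to how absences are labelled. Its size is unknown. Under assumed relabelling of 10% to 20% of intervention-arm illness days, the distortion lies between 0.54 and 1.98 points, or 12% to 44% of the target, depending on whether the true rate in that arm is 5.4% or 9.9%. The false-positive rates of 9.5% and 23.5% apply only where there is no true effect, and they rest on the planned SD and intra-cluster coefficient. No stated sample-size figure is affected.

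**What to change.** 1. In Allocation and in the Discussion, replace the blinding statements with what is true: staff record the primary outcome knowing their arm. If it is the case, add that staff and parents are not told which measure is primary. Do not present this as preventing bias, and name unblinded outcome recording as a limitation.
2. Before unblinding, pre-specify a supportive sensitivity analysis: the primary linear mixed model applied to all-cause absence (illness plus other reasons) from the existing form.
3. Report other-reason absence by arm. Interpret a fall in illness absence that is matched by a rise in other-reason absence as possible relabelling. Do not require the all-cause result to agree by a set amount, because it is supportive only.

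The cost is a change of wording, one more run of the primary model and one more line of results, with no new data. The downside is that all-cause absence is noisier, since it includes holidays and similar absences, and that it does not detect absences left unrecorded.

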### Data collection

See Table 1 for an overview of enrolment, intervention allocation, and outcome measurements.

#### Primary outcome measure

A standardised paper-based illness registration form is developed in close collaboration with the participating childcare organisation (see Additional file 3). Six booklets each comprising 2 weeks of childcare will be provided to all participating childcare groups for the study period of 12 weeks. Childcare staff will register childcare attendance, childcare absenteeism because of illness, and absenteeism due to other reasons (e.g. holiday) on a daily basis. When children are called in ill or sent home ill, childcare staff will register initials of the child, infection symptoms and how many days the child is (partially) absent due to illness. In addition, childcare staff in the intervention group will also record decision tool use. Childcare staff in both groups will receive training and feedback on registration during a 2-week run-in period before the actual start of the trial (see Table 1). This method of illness registration is comparable to other studies [63, 67, 68].

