Secondary outcomes will be measured using two different surveys on different time points and for a different target group (Table 1). Survey 1 measures number and duration of illness episodes (3), work absenteeism (4), healthcare service (5), and paracetamol. Survey 1 is only sent to parents of which the child was ill during the study period and provided informed consent. The content of this survey is in line with surveys used in previous studies [19, 34, 42, 57, 58]. Survey 2 measures knowledge, attitude, self-efficacy and risk perception among childcare staff, whereas survey 3 measures these behavioural determinants among parents. Three vignettes were included to evaluate the decision making process of childcare staff and/or parents in three different cases of ill children based on the traffic light system that was implemented in the decision tool. These surveys on knowledge, attitude, self-efficacy, and risk perception for childcare staff and parents are developed based on previous research [19, 34, 58–61]. Survey items were operationalised according theories’ definitions of behavioural determinants. Subsequently, survey items were piloted among childcare staff to check understandibility and interpretation of items [62].

**Table 1 Tab1:** Time schedule of enrolment, intervention allocation, outcome assessments

			Study period						
	Enrolment	Allocation	Post-allocation						Close-out
Timepoint	*0*	0	*T* _*1*_	*T* _*2*_	*T* _*3*_	*T* _*4*_	*T* _*5*_	*T* _*6*_	
Enrolment:	X								
Eligibility screen	X								
Informed consent Survey 1 following child’s illness episode	X	X	X	X	X	X	X	X	
Informed consent Survey 2 knowledge, attitude, self-efficacy, risk perception childcare staff	X								
Informed consent Survey 3 knowledge, attitude, self-efficacy, risk perception parents									X
Allocation		X							
Interventions:									
Educational session Childcare staff		X							
Use of decision tool + booklet Childcare staff and parents		X	X	X	X	X	X	X	
Online video Childcare staff and parents					X				
Assessments:									
Children’s illness registration		X	X	X	X	X	X	X	
Survey 1 following child’s illness episode		X	X	X	X	X	X	X	
Survey 2 Knowledge, attitude, self-efficacy, risk perception Childcare staff	X								X
Survey 3 Knowledge, attitude, self-efficacy, risk perception parents									X

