#### Survey 1 following child’s illness episode

Parents will receive an electronic survey when their child was called in ill or is sent home from childcare because of illness when parents provide consent to receive this additional survey during the 12-week study period. Parents will receive this survey within 14 days after each time their child becomes ill, followed by a total of two reminders which are sent out every 3 days.

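### Secondary outcome 2 is labelled infection incidence, but its only described source counts illnesses that lead to absence, the event the intervention targets

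*Protocol article*

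**What the plan says.** The Outcomes section of the protocol article names, as secondary outcome 2, "incidence rate of fever and common childhood infections". It attaches no condition to this outcome. The next one is restricted in its own wording: "number and duration of illness episodes in children who are called in ill or sent home because of illness during the study period". Outcomes 4 to 6 carry the same kind of restriction.

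The same section then assigns outcomes to surveys: "Survey 1 measures number and duration of illness episodes (3), work absenteeism (4), healthcare service (5), and paracetamol". Surveys 2 and 3 cover the behavioural determinants. Outcome 2 is assigned to no survey.

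That leaves the illness register described under Data collection, Primary outcome measure. Its daily part covers attendance and the reason for absence: "Childcare staff will register childcare attendance, childcare absenteeism because of illness, and absenteeism due to other reasons (e.g. holiday) on a daily basis". Symptoms come in only at a further step: "When children are called in ill or sent home ill, childcare staff will register initials of the child, infection symptoms". One item differs by arm: "childcare staff in the intervention group will also record decision tool use".

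**The concern.** The label of outcome 2 promises the rate at which children fall ill. The described source delivers the rate at which they fall ill and are absent for it. A child with a mild fever who stays for the day is logged as attending, with no symptom entry.

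In many trials this would only lower the count equally in both arms. Here the intervention acts on the recording trigger itself. The decision tool guides staff and parents on attendance, the development section treats sending febrile children home as a behaviour to be changed, and the sample size is built on a fall in illness absence. If the intervention works as intended, a smaller share of illnesses will be recorded in the intervention arm.

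Two misreadings are then possible. A lower recorded incidence could be reported as fewer infections when only exclusion changed. A real increase in infections could be masked in part or in full.

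**Working it through.** **Step 1: which sources could see an ill child who stays in care.**

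| Source | Trigger | Sees an ill child who stays? |
|---|---|---|
| Register, daily part | every childcare day | No, attendance only |
| Register, illness part | called in ill or sent home | No |
| Survey 1 | the same event, plus parental consent | No, and outcome 2 is not assigned to it |
| Surveys 2 and 3 | fixed time points | No, they cover behavioural determinants |
| Decision tool use | intervention arm only | Possibly, but with no control counterpart |

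The Survey 1 trigger reads: "Parents will receive an electronic survey when their child was called in ill or is sent home from childcare because of illness". It cannot fill the gap left by the register.

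**Step 2: the plan's own figures.** The document gives no figure for infection incidence. It does give an absenteeism target, in Sample size: control 9.9%, reduction 4.5, SD 18.035, 80% power, α 0.05 (two-sided, from Analysis).

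- The independent-samples t-test calculation gives 253.1 per group. The plan states 253.
- Clustering: 253 × (1 + (55 − 1) × 0.01) = 253 × 1.54 = 389.6. The plan states 390.
- Losses: 390 / (0.9 × 0.9) = 481.5. The plan states 482.

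These figures reproduce and are not in dispute. They show that the 4.5 is used as percentage points, so the target is 9.9 − 4.5 = 5.4%.

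**Step 3: the bias.** For each arm:

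recorded incidence = true incidence × P(absence, given illness)

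recorded ratio = true ratio × q, where q = P(absence, given illness; intervention) / P(absence, given illness; control)

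**Step 4: linking q to the target.** Absenteeism is the rate of absence episodes times the mean days absent per episode. The target ratio is r = 5.4 / 9.9 = 0.545. Let f be the share of the fall, on the log scale, that comes from fewer episodes, with the rest coming from shorter ones. With unchanged true infection, q = r^f. The document gives no value for f, so the whole range is shown. The rise that would be hidden is 1/q − 1, the true increase at which the recorded ratio is exactly 1.

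| f (assumed) | Recorded ratio, no true change | True rise hidden | Recorded ratio if the true rise is 20% |
|---|---|---|---|
| 0 | 1.000 | 0% | 1.20 |
| 0.25 | 0.859 | 16% | 1.03 |
| 0.5 | 0.739 | 35% | 0.89 |
| 0.75 | 0.635 | 58% | 0.76 |
| 1 | 0.545 | 83% | 0.65 |

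For example, at f = 0.5: q = √0.545 = 0.739, 1 / 0.739 = 1.35, and 1.2 × 0.739 = 0.89.

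**The case against.** The strongest reply is that the form itself (Additional file 3) is not shown and the article condenses a fuller protocol. The text says what is registered at an absence; it does not say that nothing else is. This stands as a limit on certainty. Still, the article does describe the register's contents, and nothing in that description covers symptoms in attending children.

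A second reply is that the abstract mentions incidence rate and duration of illness episodes together, and the Outcomes section defines episodes through absence. Outcome 2 may always have meant absence-triggered illness. If so, the defect is mainly the label. That is a fair reading, and the first remedy below meets it. The label still matters, because the restriction is written into outcomes 3 to 6 and left out of outcome 2.

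A reader might also go further than the documents allow:

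- *Outcome 2 merely repeats the primary outcome.* It does not. The primary outcome counts days and an incidence rate counts episodes; they share a trigger.
- *Recorded incidence must fall if the intervention works.* It falls only as far as absence episodes become fewer. If they only become shorter, the count is unchanged (f = 0). A child sent home part-way through a day is still recorded.
- *The arms use different recording rules.* As described, the trigger and the registration training are the same in both arms. What is expected to differ is how often an illness reaches the trigger.
- *The trial set out to monitor spread and fails to.* No such aim is stated. That this outcome cannot answer the question of spread is an inference from the design.

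**Conclusion.** The concern holds for a secondary outcome and does not touch the primary analysis or the sample size. As described, outcome 2 measures illness that leads to absence, and the comparison between arms mixes any change in infection with the intended change in exclusion. No analysis can separate the two, because symptoms in children who stay are not described as being collected.

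Over f from 0 to 1, the recorded ratio with unchanged infection runs from 1.00 to 0.55, and the true rise that would be hidden runs from 0% to 83%. At f = 0.5 the figures are 0.74 and 35%. These rest on three assumptions: the planned reduction is achieved, f lies in the range shown, and the form matches the article's description of it. The direction follows from the design whenever absence episodes become fewer; the size is illustrative only.

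**What to change.** Rename secondary outcome 2 as incidence of illness-absence episodes, and state that no conclusion about infection incidence or spread will be drawn from it. This costs nothing and removes the risk of a wrong conclusion.

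If infection incidence is wanted, add a symptom line to the daily form, identical in both arms. It would cover any child with fever or infection symptoms that day and note whether the child stayed, was sent home or was called in ill. Incidence would then be all symptomatic episodes per child-day of attendance or illness absence.

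The added line has two costs. It means some extra registration work for staff. It also brings a possible bias of its own: staff are not blinded, and intervention staff are taught that fever is usually harmless, so they may notice or log it less often in attending children. The result would still need cautious interpretation.
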